### Inclusion criteria

1. Patients listed for surgical repair of fracture neck of femur under spinal anaesthesia

2. Aged > 65 years

### Exclusion criteria

1. Planned general anaesthetic

2. Severe valvular heart disease previously shown on echocardiography (reduces reliability of monitor measurements)

3. Taking lithium (interferes with calibration of monitor)

4. Multiple injuries requiring operative management

5. Revision surgery or total hip arthroplasty for fractured neck of femur (a different patient/surgical population)

6. Not admitted to hospital through the emergency department

### Informed consent

The capacity for consent is assessed routinely by the orthopaedic team, who decide whether the patient is competent to provide consent for the surgical procedure. If they deem the patient is unable to consent for their surgery, then the patient will be deemed incapable of providing consent to enter the study, and assent from their next of kin is sought (or nominated consultee). The capacity for consent may fluctuate in the population being studied. A member of the research team also performs an additional check of the participant's ability to consent, immediately prior to starting the study. All members of the research team are trained at taking consent in accordance with ICH-GCP guidance [28].

All patients are visited postoperatively. If the patient had had a transient impairment of their ability to consent, which has subsequently resolved, retrospective consent is sought from the patient to use their data in the study. If the patient declines, date of discharge and postoperative mortality data are collected as part of routine clinical management and so will be available for analysis. The same would occur if contact with the next of kin pre-operatively had not been possible. If the next of kin subsequently declined assent, the patient data would once again be withdrawn from the study.

### Measurement of cardiac output

Monitoring of the key cardiovascular variables of blood pressure and cardiac output (volume of blood pumped by the heart per minute) is common in patients at high risk of intra-operative and postoperative complications. One such method employed is the LiDCOplus (LiDCO Ltd, Cambridge, UK). This device allows calibrated, continuous, real-time monitoring of cardiac output on a beat-to-beat basis. The LiDCOplus cardiac output method of measurement is based upon the bolus indicator dilution method of measuring cardiac output, which is the standard method of measuring cardiac output [29,30]. The only equipment required is a peripheral cannula in a vein and an arterial line (a small cannula inserted into an artery that is routinely used in high risk patients).

A small dose of lithium chloride (0.15 mmol) is injected through the venous cannula. This is a very small dose of lithium, which has no known pharmacological effect [31]. Lithium has been used for the measurement of cardiac output for many years without any side effects being reported. A lithium concentration-time curve is measured by withdrawing 5 ml of blood past a lithium sensor attached to the patient's existing arterial line and the monitor then calculates the cardiac output from the area of the primary dilution curve [32,33].

After this initial calibration, beat-to-beat measurements of cardiac output are made by analysing changes in the arterial pressure waveform. The device does not need recalibrating for at least 8 hours [29]. The LiDCOplus monitor provides values for cardiac output, systemic vascular resistance, mean arterial pressure, heart rate and left ventricle stroke volume. These are adjusted for patient weight and height. As measurements of these variables are made on a beat-to-beat basis, the LiDCOplus is an ideal device for measuring changes in cardiovascular variables to interventions such as fluid boluses.

This method of cardiac output measurement has been shown to be as accurate as the thermodilution method employed by pulmonary artery flotation (Swan-Ganz) catheters [32,33] and avoids the complications associated with their insertion and use. The LiDCOplus system is also quicker and easier to set up then than pulmonary artery catheter systems, which have previously been thought of as the gold standard of cardiac output measurement devices. The LiDCOplus monitor remains accurate even if the arterial waveform becomes over- or under-damped [34] or if regional anaesthetic techniques (such as spinal or epidural anaesthesia) are used [35].

### Study Intervention

On arrival in the anaesthetic room, all participants have an arterial line sited at the wrist using local anaesthetic and an arterial blood sample taken (to determine sodium and haemoglobin concentrations for calibration of the LiDCOplus monitor). A cannula is inserted into a peripheral vein for calibration purposes and to allow fluid administration, if there is not an adequate one already in place. The arterial line is then connected to the LiDCOplus machine and calibration performed according to the manufacturer's guidelines, using a bolus intravenous injection of lithium [36]. Routine anaesthetic monitoring is instituted by the attending anaesthetist. The spinal anaesthetic is then performed and the patient remains in the anaesthetic room for at least 10 minutes to allow collection the post-spinal anaesthetic data from the LiDCOplus monitor. The patient is then taken into theatre once the anaesthetist is satisfied that the spinal anaesthetic is adequate for surgery.

The management of fluids during the operation differs between the study group and the control group. The control group have the type, amount and rate of their intravenous fluids determined by the anaesthetist, in accordance with their usual practice. The anaesthetist is blinded to the LiDCOplus measurements by placing the LiDCO screen where it is not visible and turning off the arterial waveform display. All intra-operative fluid boluses and drugs administered by the anaesthetist, including timings, are recorded by the Investigator.

The study group have their fluids given according to the study protocol, based upon LiDCOplus measurements. The participants in this group receive a maintenance fluid of compound sodium lactate solution at a rate of 1.5 ml kg^-1 ^h ^-1^. In addition they may be given 250 ml boluses of a colloid fluid, determined by the LiDCOplus measurements of stroke volume. Fluid boluses are given until the stroke volume to achieve a sustained 10% increase from the baseline (pre-operative) readings. Further boluses are given subsequently should the stroke volume fall by clinically important amounts at any time during the operation (see Figure 1). If the attending anaesthetist feels there are clinical reasons to give more or less fluid they can do so. If blood transfusion is required packed red cells are given as the colloid. Otherwise the colloid given is at the discretion of the anaesthetist. Discretionary actions of the attending anaesthetist are recorded.

**Figure 1 F1:**
[figure not shown]
**Flow chart for administration of colloid boluses in the intervention group**. Changes in stroke volume are used to guide the administration of colloid boluses. The aim is give colloid boluses to achieve cardiac filling near the top of the Starling curve. The algorithm is interpreted in the light of clinical conditions.

The intervention is complete at the end of surgery. At this point the LiDCOplus monitoring is stopped, and the arterial cannula removed. The total amount of fluid is recorded for both groups. Postoperative fluids prescribed for participants are at the discretion of the anaesthetist.

### Standard care

All patients are admitted to dedicated trauma wards and cared for in accordance with UK 'Best Practice Tariff' [37]. This includes: assessment by orthogeriatricians; operation within 36 hours of admission; bone health assessment. All patients are cared for under a hip fracture care pathway which involves rapid assessment and admission from the emergency department; intravenous crystalloid infusions from time of admission and multiprofessional care and discharge planning. Operations are performed in dedicated trauma theatres by consultants in anaesthesia and orthopaedic trauma or senior trainees. The Queen's Medical Centre has undertaken continuous, systematic audit of its hip fracture care since 2001 [22-24].

### Cost Analysis

Data on cost of treatment will be calculated from drug use, investigations (diagnostic imaging, ECGs, blood tests) and from the clinical record, which includes standardised costs for physiotherapy, occupational therapy and discharge planning. The cost of additional monitoring required for each patient will also be taken into consideration in the cost analysis. Data will be presented in terms of total non-operative costs, costs per day and excess costs attributable to treatment group.

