**Methods:**

Single-centre randomised controlled parallel group trial. Randomisation by website using computer generated concealed tables. Setting: University hospital in UK. Participants: 128 patients with acute primary hip fracture listed for operative repair under spinal anaesthesia and aged > 65 years. Intervention: Stroke volume guided intra-operative fluid management. Continuous measurement of SV recorded by a calibrated cardiac output monitor (LiDCOplus). Maintenance fluid and 250 ml colloid boluses given to achieve sustained 10% increases in stroke volume. Control group: fluid administration at the responsible (blinded) anaesthetist's discretion. The intervention terminates at the end of the surgical procedure and post-operative fluid management is at the responsible anaesthetist's discretion. Primary outcome: length of acute hospital stay is determined by a blinded team of clinicians. Secondary outcomes include number of complications and total cost of care.

Funding NIHR/RfPB: PB-PG-0407-13073.

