#### Secondary Aims

2) To investigate if using SV guided fluid therapy a patient receives while having their fractured hip repaired under a spinal anaesthetic affects:

a. the time until the patient is medically well enough to be discharged from hospital;

b. the number of postoperative complications;

c. the total amount of intravenous fluid given during surgery;

d. the total cost of care.

3) To characterise the changes in the way the heart and blood vessels work after a spinal anaesthetic, as measured by minimally-invasive cardiac output monitoring.

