The potential implications of our results are important. Approximately 80,000 patients per year undergo hip fracture surgery in the UK. Ward costs contribute 84% of the total cost of hospital expenditure of patients undergoing such a procedure, at a rate £430 per patient per day [45]. If stroke volume guided fluid management results in a reduction in hospital stay of 5 days, as demonstrated using the Doppler ultrasound probe [13,14], the saving could be around £2,150 per patient. This equates to a potential national saving in the UK of around £150 million per year. The reduction in duration of hospital stay is therefore one potential way of minimising expenditure following hip fracture.

Hip fracture is likely to become an increasing health issue within the UK [6,7], with associated economic implications, and a high mortality and morbidity allied to patients who suffer such injury. Despite this there is a limited evidence base with regards to guidance of best practice. Our study aims to augment this evidence base and improve the peri-operative management of patients presenting with fractured hip.

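### The cost analysis does not match the stated outcome: it presents a non-operative total, names no ward cost, and gives no rule for attributing the monitor to an arm

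*Protocol article*

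**What the plan says.** Secondary Aims asks whether stroke volume guided fluid therapy affects "the total cost of care", and the Abstract (Methods) agrees: "Secondary outcomes include number of complications and total cost of care".

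Cost Analysis then describes the calculation: "Data on cost of treatment will be calculated from drug use, investigations (diagnostic imaging, ECGs, blood tests) and from the clinical record". The clinical record is said to supply standard costs for physiotherapy, occupational therapy and discharge planning. The section adds: "The cost of additional monitoring required for each patient will also be taken into consideration in the cost analysis". It closes with the outputs: "Data will be presented in terms of total non-operative costs, costs per day and excess costs attributable to treatment group".

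Three other places bear on this.

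- Study Intervention: fluid management differs between arms only during the operation, and the intervention stops when surgery ends.
- Study Intervention: "all participants have an arterial line sited at the wrist using local anaesthetic and an arterial blood sample taken". The LiDCOplus is connected and calibrated in everyone. In controls it runs with the screen out of the anaesthetist's sight.
- Discussion: "Ward costs contribute 84% of the total cost of hospital expenditure of patients undergoing such a procedure", at £430 per patient per day.

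**The concern.** The stated output is narrower than the stated outcome in two ways, and a third item is left open.

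1. **Operative phase.** A non-operative total, taken at its word, leaves out the phase in which the two arms are treated differently, including the fluids that are the intervention.
2. **Ward cost.** No ward or bed-day cost appears among the items named. By the article's own figures this is the largest part of hospital cost, and it is the part that a shorter stay would reduce.
3. **Monitoring.** The monitoring cost is brought in, but both arms receive it and nothing says how it counts towards the excess cost of the intervention.

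If the section were followed literally, the reported total could miss most of any saving from a shorter stay and some of what the intervention consumes. Depending on how monitoring is charged, the excess cost could also omit the technology under evaluation. Readers would still take the figure for the total cost of care.

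**Working it through.** **Inputs.** Ward rate £430 per day and ward share 84% (Discussion); mean acute stay 17 days and design effect 3 days (Sample size and justification); 5-day saving (Discussion); 26-day median stay and £25,424 per patient (Background). No monitoring cost is given.

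**The article's own figure.** Saving per patient = days saved x daily rate = 5 x £430 = £2,150, as stated. (The national figure of about £150 million follows from 70,000 patients, £150.5 million, not from the 80,000 in the same paragraph, £172.0 million. This does not affect the point here.) The projected saving is therefore made up entirely of ward days.

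**Design effect in ward cost.** 3 x £430 = £1,290 per patient.

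**Illustrative split of a 17-day stay**, assuming the £430 rate and the 84% share both apply to it:

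- ward cost = 17 x £430 = £7,310
- total = £7,310 / 0.84 = £8,702
- non-ward cost = £8,702 - £7,310 = £1,392

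**What would be seen if ward cost were left out:**

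- If non-ward cost falls in proportion to stay: £1,392 x 3/17 = £246, out of £246 + £1,290 = £1,536, that is 16%.
- If non-ward cost does not depend on stay: £0 of £1,290.

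**Sensitivity of the split.** At 12 days the non-ward cost is 12 x £430 / 0.84 - £5,160 = £983. At 26 days it is 26 x £430 / 0.84 - £11,180 = £2,130. The Background figure would give 16% of £25,424 = £4,068, but its scope is not stated. The £1,392 is thus one value in a wide range.

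**Monitoring.** Let m be the cost per patient of monitor, line and calibration. Charged as used, the between-arm difference is m - m = 0. Charged to the intervention arm only, it is m - 0 = m. The article does not say which applies.

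**The case against.** The strongest reply is that silence is not exclusion. A journal article condenses, the list of items drawn from the clinical record is not presented as closed, and a cost per day is among the outputs, so days are evidently in view. This stands: ward days are unnamed, and a reader who infers that they are excluded goes beyond the text. It does not remove the mismatch, because the non-operative total is a stated output that conflicts with a stated outcome.

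Second, operative cost is not wholly left out. Monitoring is added explicitly, and drug use is not limited to the ward. Operative costs common to both arms would also cancel in the difference. This too stands, but the fluids are not common to both arms, and they are not named.

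Third, a reader might infer that the monitoring difference is zero under the plan. Nothing says that both arms are charged alike. The wording on additional monitoring could mean only what the strategy needs beyond usual care. The text leaves this open.

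Fourth, a reader might infer that the Discussion's economic argument could not be tested. It can: that argument is days saved times a daily rate, and the trial measures length of stay.

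Finally, cost per day may rise when stay shortens, because fixed costs are spread over fewer days. It is one of three outputs and is not named as the basis for comparing arms, so planning it is no error.

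**Conclusion.** The concern holds as a mismatch to be reconciled. Cost Analysis presents a non-operative total for an intra-operative intervention and names no ward cost, while the outcome is the total cost of care. It would be too strong to say that the analysis cannot answer the aim, since the component list may be condensed.

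The size is illustrative: £1,290 per patient in ward cost for the 3-day design effect, assuming that the £430 rate applies at this unit and that ward days are indeed not costed. The £1,392 non-ward figure is not an upper bound. The effect of monitoring on the excess cost cannot be sized, because no unit cost is given.

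The outcome is secondary. The primary analysis and the sample size are untouched.

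**What to change.** Amend Cost Analysis as follows.

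- **Scope.** Define total cost as bed-day cost x acute length of stay, plus recorded intra-operative fluids and drugs, plus the items already listed. Either drop the restriction to non-operative costs or report that figure under its own name beside the total.
- **Attribution.** State that LiDCOplus, arterial line and calibration are charged to the intervention arm only when the excess cost is computed, because in controls they serve the research and cannot guide fluids. The article describes arterial lines as routine in high-risk patients. If some controls would have had one anyway, charging the line this way somewhat overstates its share of the excess.
- **Cost per day.** It may stay as a descriptive figure.

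**Cost of the change.** Mainly wording and a little more analysis. Discharge data are collected routinely, and intra-operative fluids and drugs are recorded in the trial. Wider theatre resource use is not shown to be collected, so it is not asked for here. The downside is that the intervention will look somewhat dearer per patient than if monitoring were charged as used.

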### Statistics

Data will be analysed by the research team in conjunction with a medical statistician, using latest versions of StatXact software. There will be no interim analysis.

From previous examination of the Nottingham Hip Fracture Database (which has over 7000 patients) it is expected that the primary outcome, length of stay (LOS), will be normally distributed following a log transformation. Following transformation these data will be analysed using ANOVA using the stratification risk categories. The primary outcome measure is time until declared medically fit for discharge. Length of acute hospital stay, superspell (total time in hospital including rehabilitation) will be analysed similarly.

The secondary outcomes of complications, residence and place of discharge will be treated as categorical and differences between the groups will be examined using loglinear analysis. Mortality outcome will be analysed using Kaplan-Meier mortality curves and log rank tests..

All secondary variables will the presented using descriptive statistics. In addition to the calculated values, confidence intervals and odds-ratios will be presented when appropriate. All clinical information including all adverse events will be presented in full. All secondary analyses will be interpreted with caution as the sample size calculation is based on the primary outcomes only. However, the level of power associated with secondary results will be investigated.

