### Randomization and Blinding

Randomisation (on a one-to-one allocation basis) is via a password-protected web based randomisation service provided by the Clinical Trials Support Unit and the sequence not revealed until datalock. To achieve similar numbers and balance on risk, patients will be stratified according to predicted 30-day mortality (2 levels). The Nottingham Hip Fracture Score [22-24], is used to identify patients with low (≤ 10%) or high (> 10%) risk of mortality within 30-days. Subjects are randomised on arrival in the anaesthetic room to minimise the risk of medical or surgical cancellation after randomisation.

Patients, orthopaedic surgeons and ward staff are blinded to the treatment intervention. The operative attending anaesthetist is not blinded to the treatment arm, but is blinded to the cardiac output measurements for the control arm. Postoperative data collection is by a research nurse blinded to treatment allocation. The decision that a patient is medically fit for discharge is made by the multiprofessional team when all are satisfied that the participant has no ongoing needs for acute hospital care. This team is blinded to participant allocation.

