### Sample size and justification

Previous studies of optimisation strategies have demonstrated approximately 30% reduction on acute length of stay or time until medically fit to discharge and approaches towards 50% reductions in complications in survivors.

Length of acute hospital stay in our unit is consistently around 17 days (SD 4.9 days), so to find a 3 day reduction in LOS in survivors would require 58 patients in each group with 90% power and α = 0.05. Assuming a 10% drop out rate (conversion to general anaesthesia, operative cancellation after randomisation etc.) we aim to randomize 64 subjects in each group. This would also provide the same power to find a 50% reduction in complication rates between the two groups. The study will not be powered to demonstrate differences in mortality (a 50% reduction in 30-day mortality from 10% to 5%, would require around 450 patients in each group).

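### The primary ANOVA adjusts for the Nottingham Hip Fracture Score only as a two-level stratum; adding the score itself could gain a little precision if it predicts the outcome

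*Protocol article*

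**What the plan says.** The Statistics section of the protocol article expects that length of stay "will be normally distributed following a log transformation". It then gives the primary model: "Following transformation these data will be analysed using ANOVA using the stratification risk categories". No other covariate is named for that analysis.

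Randomization and Blinding defines the categories. Allocation is stratified on two levels of predicted 30-day mortality, and the Nottingham Hip Fracture Score "is used to identify patients with low (≤ 10%) or high (> 10%) risk of mortality within 30-days". The article does not say in words that the numeric score is kept in the trial dataset. Each patient must nevertheless have a score before randomisation to be placed in a stratum.

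Sample size and justification takes a mean stay of about 17 days with SD 4.9 days and states that "to find a 3 day reduction in LOS in survivors would require 58 patients in each group with 90% power and α = 0.05". This calculation takes no credit for covariate adjustment.

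**The concern.** The stated model keeps only which side of the 10% cut a patient falls on. Two patients just either side of the cut are treated as different, and two patients far apart within one stratum are treated as alike. If the score is related to the outcome within strata, that variation stays in the residual error and the treatment effect is estimated less precisely than the available baseline data would allow.

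The article gives qualitative reasons to expect some relation. Its Recruitment section says that confused patients both die more often and stay longer. Its Discussion lists pre-fracture morbidity and mobility among the influences on length of stay and time to medical fitness. What is at stake is the width of the confidence interval in a trial of 128 patients, not the validity of the comparison.

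**Working it through.** **1. The plan's own figure.** Inputs from Sample size and justification: difference 3 days, SD 4.9 days, power 90%, α = 0.05 (taken as two-sided). Normal approximation:

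n per group = 2 × (1.960 + 1.282)² × 4.9² / 3² = 2 × 10.507 × 24.01 / 9 = 56.1, so 57.

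The exact t-test gives 57.04, so 58. The stated 58 is reproduced with no adjustment at all. Power at 58 per group is 90.9% (normal) or 90.5% (t-test). A one-sided test would need only 46 and does not fit.

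**2. Share of explained variance kept by a two-level cut.** Let p be the share of patients at high risk, z the matching normal quantile and φ the normal density. For a normal score that is linear in the outcome:

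k = φ(z)² / (p(1 − p))

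- p = 0.5: 0.3989² / 0.25 = 0.637
- p = 0.2: 0.2800² / 0.16 = 0.490

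The documents do not give p. The range 0.2-0.5 is an assumption.

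**3. Gain from using the score itself.** Let r be the correlation of the score with the log outcome, which the documents also do not give. As a fraction of total variance, the residual variance is 1 − k·r² with the two-level factor and 1 − r² with the score in the model. Under linearity the stratum adds nothing further once the score is in. So:

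gain in effective sample size = (1 − k·r²) / (1 − r²) − 1

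Patients' worth is the gain times 116 (2 × 58 evaluable). Power is at 58 per group, normal approximation.

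| r | Gain, p = 0.5 | Gain, p = 0.2 | Patients' worth | Power, two-level | Power, score |
|---|---|---|---|---|---|
| 0 | 0 | 0 | 0 | 90.9% | 90.9% |
| 0.2 | 0.9745/0.96 − 1 = 1.5% | 0.9804/0.96 − 1 = 2.1% | about 2 | 91.5-91.6% | 92.0% |
| 0.3 | 0.9427/0.91 − 1 = 3.6% | 0.9559/0.91 − 1 = 5.0% | 4-6 | 92.1-92.4% | 93.3% |
| 0.4 | 0.8981/0.84 − 1 = 6.9% | 0.9216/0.84 − 1 = 9.7% | 8-11 | 93.0-93.6% | 94.9% |
| 0.5 | 0.8408/0.75 − 1 = 12.1% | 0.8775/0.75 − 1 = 17.0% | 14-20 | 94.1-94.9% | 96.8% |

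If only 10% were at high risk, k would fall to 0.342 and the gains at r = 0.2 and 0.3 would be 0.98632/0.96 − 1 = 2.7% and 0.96922/0.91 − 1 = 6.5%.

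**4. Cost if the score is uninformative.** With 116 evaluable patients, residual degrees of freedom fall from 116 − 3 = 113 to 112.

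**5. Scale.** The power figures use the day scale of the sample size section, whereas the analysis is on the log scale. The relative gains apply on whichever scale r is measured.

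**The case against.** The strongest reply is that nothing here is wrong. Analysing by the stratification factor matches the randomisation, and the stated 58 per group holds with no covariate at all, so the two-level factor can hardly do other than help. Further covariates are often left to a fuller analysis plan, which is not shown. All of this stands, except that the article does state the primary model and its adjustment, so improving that statement is a fair comment.

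A reader might infer that precision is certainly lost. The documents do not support this. They introduce the score only as a predictor of 30-day mortality and report no correlation with length of stay or time to medical fitness. Early deaths could shorten stay in high-risk patients and weaken or reverse the relation: the sample size is reasoned for survivors, but the Full Analysis set is not restricted to them. The Discussion also stresses non-clinical influences on stay.

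A reader might also infer that most of the score's information is thrown away, or that some 20 patients' worth is at stake. On the assumptions above the cut keeps about half to nearly two thirds of the explainable variance. The figure of 20 needs r = 0.5 together with a 20% high-risk share, and nothing in the article supports a correlation that high.

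Finally, the shares kept rest on a normal, linear score, and the article describes neither the score's scale nor its distribution.

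**Conclusion.** The point holds as a minor, conditional efficiency improvement. The primary model is valid and the planned power is unaffected. If the score predicts the log outcome with r of 0.2-0.3, adding it is worth about 1.5-5% in effective sample size, or 0.4-1.2 power points at 58 per group. The gain reaches 12-17% only at r = 0.5 and is nil at r = 0. These figures assume 20-50% of patients at high risk, a normal score linear in the log outcome, and a numeric score that is retrievable for every randomised patient. The first two are not given in the article. The third is a reasonable inference from the stratification.

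**What to change.** Before datalock, prespecify the primary model as ANCOVA on the log-transformed primary outcome, with treatment, the randomisation risk category and the Nottingham Hip Fracture Score as a linear covariate. Keeping the risk category means that the analysis still reflects the stratified randomisation.

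Two things should be settled first:

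- **Which outcome is primary.** The Abstract and Primary Aims name length of acute stay, the Statistics section also names time until declared medically fit, and the Discussion treats both as primary. The model should refer to whichever is confirmed.
- **Whether the score is prognostic.** The unit's database of over 7000 patients, cited in the Statistics section, can be used to check the correlation and its linearity without touching trial outcomes. If the relation is negligible, the stated model can stay as it is.

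The cost is one line in the analysis plan, confirmation that the numeric score is held for each patient, and one degree of freedom if the score turns out not to predict the outcome. The article plans no interim analysis and withholds the allocation sequence until datalock, so the choice can still be made without knowledge of results by arm.
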